### Training and certification on neurological assessment

The success of the trial recruitment depends on training and certification of all front-line clinical staff at the recruiting sites on expanded modified Sarnat staging (Table 1) [30]. The training will involve a lecture explaining the Sarnat staging, animated and actual videos of the neurological examination as well as post-training evaluation and certification. The entire training can be completed over 90 min using a fully virtual platform. The training will be repeated on an annual basis. In addition, monthly feedback on the neurological assessments of all screened and recruited neonates will be provided to each site to ensure quality assurance.

**Table 1 Tab1:**
[figure not shown]
Certification form on the expanded modified Sarnat staging based on the NICHD neonatal research network hypothermia trials [22]

### Withdrawal criteria

Neonates will be withdrawn from the study if either parents withdraw consent or due to the clinician’s decision at any time. A withdrawal form will be filled in and consent will be obtained for use of the data collected up to the withdrawal from the trial. Discontinuation of the study intervention for a serious adverse event will be at the discretion of the attending physician in consultation with the site principal investigator. The neonate will continue to be part of the study as per the intent-to-treat principle.

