## Study design

### Setting

Cooling in mild encephalopathy (COMET) is a phase III multi-centre open label two-arm randomised controlled trial (RCT) with internal pilot and masked outcome assessments. Administration of cooling therapy cannot be masked. The trial will recruit from five neonatal operational delivery networks (ODN) involving around 50 to 60 NHS hospitals. The recruitment will occur at both tertiary and non-tertiary (non-cooling) centres, although the neonates recruited from non-tertiary centres will be transferred to a tertiary centre after randomisation.

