### Assessment and follow-up

The follow-up assessment will be done when the recruited babies are 24 (± 2) months of age, by a central team of 2 to 4 examiners, masked to the trial group allocation. The assessment will be carried out using the Bayley Scales of Infant and Toddler Development IV. This is a formal examiner administered age-standardised test that assesses development in three domains: cognition, language, and motor development. In addition, all neonates will have a detailed neurological examination, including Gross Motor Function Classification System (GMFCS) for cerebral palsy, vision, and hearing assessment.

Each assessor will be trained by the test publisher (Pearson UK) and certified against the COMET gold standard examiner prior to the assessments being conducted. The examiners will be re-certified against the gold standard examiner annually to reduce interobserver variability to 10%. Vision and auditory status of neonates will be collected as part of the medical history. The follow up visit will be scheduled in close consultation with the parents, either at the local hospital or at home. Appropriate travel expenses will be provided for families for the visit. Travel expenses will also be provided/reimbursed to research team members who must travel to perform the follow up examination.

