### Recordings and reporting of SAEs, SARs and SUSARS

Safety outcomes will consist of measurements of Adverse Events (AEs) and Serious Adverse Events (SAEs) (see section below). If there are sufficient numbers of AEs and SAEs, the Chi-square test or Fisher’s exact test will be used to compare the number of patients with these outcomes between groups. The Mann-Whitney test will be used to compare the number of AEs/SAEs between groups. A list of individual AEs will be reported in each group. All analysis will be performed on a modified Intention to Treat (mITT) basis, using patients with valid outcome data in the analysis. Neonates will be analysed in the groups to which they were randomised (intent-to-treat analysis), regardless of the treatment received.

Monitoring for adverse events of whole-body hypothermia in the intervention group during the intervention period and both groups during the entire length of hospital stay will be conducted by evaluating events described in the secondary outcomes. An additional safety measure will be the appointment of an external Independent Data Monitoring Committee (IDMC) where the progress of the trial and adverse events (AE) will be closely monitored at 4 to 6 monthly intervals, masked to the allocation. The IDMC charter will be finalised and signoff before the start of recruitment.

**The adverse events** will include persistent metabolic acidosis, thrombosis, major bleeding, perforations/ulcerations/bleeding from the rectal probe, hyperglycaemia, hypoglycaemia, necrotising enterocolitis (NEC), thrombocytopenia requiring platelet transfusions, coagulopathy requiring blood products, loss of skin integrity, and hypotension requiring more than 2 inotropes.

**Serious adverse events (SAE)** will include mortality, major cerebral bleeds on MRI, pulmonary bleeds, PPHN requiring inhaled nitric oxide or extra-corporeal membrane oxygenator (ECMO), or any other clinical event the investigators deem as life threatening. Additional SAE reports may be requested (e.g., monthly) throughout the course of the study. Safety will be assessed by the frequency of SAE, and total number of events per baby.

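### A clinician's decision can withdraw a baby from the study itself, not only from the intervention, which sits badly with the promised as-randomised analysis

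*Protocol article*

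**What the plan says.** The Withdrawal criteria section of the protocol article contains two rules with different objects.

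- **Leaving the study.** "Neonates will be withdrawn from the study if either parents withdraw consent or due to the clinician’s decision at any time". A withdrawal form is completed, and "consent will be obtained for use of the data collected up to the withdrawal from the trial".
- **Stopping the intervention.** "Discontinuation of the study intervention for a serious adverse event will be at the discretion of the attending physician", who is to consult the site's lead investigator. The next sentence reads "The neonate will continue to be part of the study as per the intent-to-treat principle".

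The analysis statements are in the section on recording and reporting of SAEs, SARs and SUSARs, but the first is worded to cover every analysis: "All analysis will be performed on a modified Intention to Treat (mITT) basis, using patients with valid outcome data in the analysis". It is followed by "Neonates will be analysed in the groups to which they were randomised (intent-to-treat analysis), regardless of the treatment received".

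Two other facts matter. Under Setting: "Administration of cooling therapy cannot be masked". Under Assessment and follow-up: "The follow-up assessment will be done when the recruited babies are 24 (± 2) months of age".

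**The concern.** Stopping an allocated treatment and leaving a trial are different events. The first is compatible with intention to treat, because the baby is still followed and counted. The second ends data collection. The first rule puts a clinician's decision on the same footing as parental withdrawal of consent, sets no criteria, and applies at any time up to the 24-month visit.

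A baby removed before that visit has no Bayley-IV score and falls outside the set with valid outcome data. The clinician who decides is likely to know the arm, and the decision may reflect how the baby is doing. If such decisions were more common in one arm, or were made for different reasons in each arm, the babies analysed would no longer be the groups that randomisation created. Masked assessment at 24 months does not protect against this, because the loss comes before it. No later analysis can recover a score that was never collected.

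**Working it through.** **1. The plan's own figures (Sample size calculation).** Inputs: SD 15, difference 5 points, significance level 0.05 (taken as two-sided), power 90%.

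- Normal formula: n = 2 × (1.960 + 1.282)² × 15² / 5² ≈ 189.1, so 190 per group. The t-based calculation gives 190.1, so 191, as stated.
- Drop-out: 382 / 0.90 = 424.4, so 425, or 426 for equal arms, as stated.
- Power by t-test at 10, 12.5, 15, 17.5 and 20% drop-out: 90.2, 89.4, 88.6, 87.6 and 86.6%. Table 3 gives 90.0, 89.4, 88.5, 87.7 and 86.5%.

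These figures hold and are not in dispute. They describe loss of power when babies are missing. They say nothing about bias when the missing babies differ from those who remain.

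**2. The path from the rule to the primary analysis.**

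- Withdrawal criteria: a clinician's decision takes the baby out of the study.
- Assessment and follow-up: the outcome is measured at 24 (± 2) months, so a baby withdrawn earlier has no score.
- Analysis statement: only babies with valid outcome data are analysed, so that baby is not in the comparison.
- Setting: treatment is not masked, so the decision can be influenced by arm.

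**3. Size, as an illustration.** The document gives no rate of clinician withdrawal and no expected score for such babies, so both are assumptions. Let w be the share of one arm withdrawn and k the amount by which their mean would lie below that arm's full mean. With full mean m and mean r of those remaining, m = w(m − k) + (1 − w)r, so the bias is r − m = wk / (1 − w).

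| w | k = 10 | k = 15 | k = 20 |
|---|---|---|---|
| 2% | 0.20 | 0.31 | 0.41 |
| 5% | 0.53 | 0.79 | 1.05 |
| 10% | 1.11 | 1.67 | 2.22 |

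If the shortfall is measured from the babies who remain, the bias is w × k: 0.05 × 10 = 0.5 and 0.05 × 20 = 1.0. The 5% case is therefore about 0.5 to 1.1 points, or roughly 10 to 20% of the 5-point target. It raises the mean of whichever arm loses the babies.

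**4. Effect on type I error with no true difference.** With 191 per arm, SE = 15 × √(2/191) ≈ 1.53. By normal approximation, a bias of 0.8 points raises the two-sided error from 5% to about 8%. A bias of 1.67 points (10% of one arm, all 15 points lower on average) raises it to about 19%.

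**5. The score of 54.** The Primary outcome section assigns 54 to babies who die or are too disabled to be tested, so that the worst outcomes count. The article does not say whether a baby withdrawn beforehand would still receive it. If not, and if the arm mean is 100 (the normative mean, an assumption here), losing one such baby from 191 raises the arm mean by (100 − 54)/190 ≈ 0.24 points.

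**The case against.** Several stronger readings are tempting, and the document does not support them.

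- **That the rule flatly contradicts intention to treat.** The sentence "The neonate will continue to be part of the study as per the intent-to-treat principle" follows, and literally covers, stopping the intervention for a serious adverse event. The analysis statement declares a modified intention-to-treat set and so openly accepts missing outcomes. The accurate word is tension, between the clinician-withdrawal rule and the promise to analyse as randomised.
- **That babies with seizures, or controls who are later cooled, will be withdrawn.** The Normothermia section allows clinical cooling of some controls without mentioning withdrawal, and the analysis statement keeps them in their randomised arm.
- **That exclusions will occur, differ by arm and fall on the sickest babies.** Nothing shows this. The article expects about 5% seizures in both groups, so that figure does not support a 5% loss from one arm. It also cites more than 97% follow-up in previous UK trials. A loss of 5% from one arm is 2.5% of the trial, which would be nearly all of a 3% total loss.

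It can also be said that the consent step for data up to withdrawal fits parental withdrawal most naturally, and that the withdrawal form or the manual of procedures, neither of which is shown, may separate levels of withdrawal. Both points are fair and lower the severity. They do not remove the point. The published rule states expressly that the clinician's decision withdraws the baby from the study, and the same section uses a different term for stopping the intervention. This is a stated rule, not a detail left to another document.

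**Conclusion.** The point holds as a defect in a stated rule. An unmasked clinician may, without stated criteria and at any time before the 24-month assessment, remove a baby from the study, and the analysis set then omits that baby. This permits exclusions after randomisation that could relate to arm and prognosis, and it weakens the as-randomised comparison.

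The size is unknown. The range of about 0.5 to 1.1 points rests on two assumptions that the document does not supply: that 5% of one arm and none of the other is withdrawn, and that those babies would have scored 10 to 20 points lower. At 2% the bias is 0.2 to 0.4 points. If clinician withdrawals are rare, or similar in number and kind in both arms, the bias is small. The 10% drop-out allowance protects power but does not address this bias.

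Severity: should be fixed. The document does not support calling it a must-fix.

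**What to change.** Reconcile the first sentence of the Withdrawal criteria with the intention-to-treat statements in that section and in the analysis text:

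- A clinician's decision does not end study participation or follow-up.
- Only parental withdrawal of consent ends follow-up.
- For every other randomised baby, the 24-month Bayley-IV is sought and analysed in the randomised group.
- The withdrawal form records stopping the intervention separately from stopping follow-up.

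The existing rule on when the intervention may be discontinued is a clinical matter and should be left unchanged.

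The cost is one amended sentence and a form with two fields in place of one. Sample size, outcomes and schedule are unaffected, and retention can only gain.

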### Assessment and follow-up

The follow-up assessment will be done when the recruited babies are 24 (± 2) months of age, by a central team of 2 to 4 examiners, masked to the trial group allocation. The assessment will be carried out using the Bayley Scales of Infant and Toddler Development IV. This is a formal examiner administered age-standardised test that assesses development in three domains: cognition, language, and motor development. In addition, all neonates will have a detailed neurological examination, including Gross Motor Function Classification System (GMFCS) for cerebral palsy, vision, and hearing assessment.

Each assessor will be trained by the test publisher (Pearson UK) and certified against the COMET gold standard examiner prior to the assessments being conducted. The examiners will be re-certified against the gold standard examiner annually to reduce interobserver variability to 10%. Vision and auditory status of neonates will be collected as part of the medical history. The follow up visit will be scheduled in close consultation with the parents, either at the local hospital or at home. Appropriate travel expenses will be provided for families for the visit. Travel expenses will also be provided/reimbursed to research team members who must travel to perform the follow up examination.

### Primary outcome

The primary outcome is the mean Cognitive Composite Scale score from the Bayley IV examination at 24 (*±* 2) months of age. The RCTs of hypothermia for moderate or severe encephalopathy have used the composite outcome of death or disability because of high mortality rates, whereas mortality is expected to be low in mild encephalopathy. Therefore, a continuous numerical developmental score among survivors will be more robust to detect treatment effects than categorical outcomes and hence was selected as the primary outcome.

Babies who die (the mortality rate is expected to be less than 1% in mild HIE) or who cannot be assessed with the Bayley-IV due to severe disability (also anticipated to be low in frequency) will be allocated a Cognitive Scale Composite score one point below the basal test score (i.e., score of 54) [31, 32].

If the child is too tired to co-operate with the Bayley assessment at the time of the original appointment, the assessment will be re-scheduled and performed at a place more suitable for the child, for example at home, within the window period of assessment.

### Secondary outcomes

Outcomes assessed during neonatal hospitalisation:

Seizures (clinical and aEEG confirmed).Duration of intensive care defined as number of days of neonatal intensive care.Duration of hospital stay defined as the total number of days of inpatient care in a neonatal unit.Duration of mechanical ventilation defined as number of hours on invasive ventilation through an endotracheal tube.Duration of inotropic support defined as total number of hours on inotropic support.Bloodstream or cerebrospinal fluid positive infection defined as isolation of a pathogenic organism from blood or cerebrospinal fluid along with a clinical diagnosis of sepsis, at any time during neonatal hospitalisation.Thrombocytopenia or coagulopathy requiring transfusion of blood products.Successful breastfeeding (at hospital discharge).Brain injury scores on conventional magnetic resonance imaging.

Longer term secondary outcomes assessed at 24 (*±* 2) months include:

Survival without any neurological impairment defined as a score of *≥* 85 in all Bayley-IV domains (motor, language, and cognitive), normal neurological examination with no cerebral palsy (Gross motor function classification system score 0), no hearing or visual impairment (as reported by parents), and no seizure disorder.Preschool Child Behaviour Checklist (CBCL 1½-5) will be completed by parents at the 24(*±* 2) month assessment to provide a standardised measure of children’s behavioural outcomes on scales that assess internalizing and externalizing behaviour problems and a Total Problems Scale. Mean standardised T-scores on each scale will be compared between groups. The CBCL checklist will be completed after the Bayley IV assessments.Cerebral palsy with a gross motor function classification system score (GMFCS) of 2 or more.Head circumference of less than 2 standard deviations.

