**Methods:**

The COMET trial is a phase III multicentre open label two-arm randomised controlled trial with masked outcome assessments. A total of 426 neonates with mild encephalopathy will be recruited from 50 to 60 NHS hospitals over 2 ½ years following parental consent. The neonates will be randomised to 72 h of whole-body hypothermia (33.5 *±* 0.5 C) or normothermia (37.0 *±* 0.5 C) within six hours or age. Prior to the recruitment front line clinical staff will be trained and certified on expanded modified Sarnat staging for encephalopathy. The neurological assessment of all screened and recruited cases will be video recorded and centrally assessed for quality assurance. If recruitment occurs at a non-cooling centre, neonates in both arms will be transferred to a cooling centre for continued care, after randomisation. All neonates will have continuous amplitude integrated electroencephalography (aEEG) at least for the first 48 h to monitor for seizures. Predefined safety outcomes will be documented, and data collected to assess resource utilization of health care. A central team masked to trial group allocation will assess neurodevelopmental outcomes at 2 years of age. The primary outcome is mean difference in composite cognitive scores on Bayley scales of Infant and Toddler development 4th Edition.

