### Health economic evaluation

A prospective health economic evaluation will be embedded within the trial design. The health economic evaluation will adopt a UK NHS and Personal Social Services perspective in accordance with the National Institute for Health and Care Excellence (NICE) Reference Case [33].

Primary research methods designed will mirror those applied in our economic evaluation conducted as part of the TOBY trial [34], and will include capital and non-capital costs of the whole-body hypothermia system, transport costs to tertiary cooling centres, and length of hospital stay. Downstream resource consequences until hospital discharge, including duration and intensity of care provided, will be captured through trial case report forms. In addition, online economic questionnaires completed by parents at 6, 12, 18, and 24 months will document post-hospitalisation resource utilisation. Unit costs for post-hospital discharge resource inputs will largely be derived from national reference tariffs, although primary research that uses established accounting methods may also be required.

The cost-effectiveness of whole-body hypothermia will be expressed in terms of incremental cost per unit change in the cognitive composite score of the Bayley-III examination (cost-effectiveness analysis). Bivariate regression of costs and consequences, with multiple imputations of missing data, will be conducted to generate within-trial estimates of incremental cost-effectiveness associated with whole body cooling. Sensitivity analyses will be undertaken to assess the impact of areas of uncertainty surrounding components of the economic evaluation. The sensitivity analyses will include re-estimation of cost-effectiveness based on cases with complete data, and re-estimation of cost-effectiveness assuming a broader societal perspective. The latter will incorporate direct costs borne by families and friends, for example, travel costs, economic values for informal care provided by family and friends, and economic values associated with productivity losses; the values of these broader resource consequences will be informed by responses to questions in the online parent-completed questionnaires. Cost-effectiveness acceptability curves will be used to show the probability of cost-effectiveness of whole-body hypothermia at alternative cost-effectiveness thresholds with plausible economic values associated with improvements in cognition informed by a literature review.

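### Hearing and vision in the 24-month impairment-free survival outcome are given three different sources, and the one that scores the outcome is parent report, which is not masked

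*Protocol article*

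**What the plan says.** All references are to the Protocol article.

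Assessment and follow-up says that the 24-month visit is done "by a central team of 2 to 4 examiners, masked to the trial group allocation". It goes on to say that "all neonates will have a detailed neurological examination, including Gross Motor Function Classification System (GMFCS) for cerebral palsy, vision, and hearing assessment". The next paragraph of the same section gives another source: "Vision and auditory status of neonates will be collected as part of the medical history".

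Secondary outcomes defines survival without any neurological impairment. A child must score at least 85 in every Bayley-IV domain, have a normal neurological examination without cerebral palsy, have no seizure disorder, and have "no hearing or visual impairment (as reported by parents").

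Setting describes an open-label trial and states that "Administration of cooling therapy cannot be masked". Under Randomisation and trial intervention, parents consent before randomisation. The abstract (Methods) summarises follow-up thus: "A central team masked to trial group allocation will assess neurodevelopmental outcomes at 2 years of age".

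Secondary outcomes also has the parent-completed behaviour checklist (CBCL) filled in after the Bayley-IV. No position in the visit is given for the medical history.

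**The concern.** The same component has three descriptions: an item in the masked team's examination, an item of medical history, and a parent's report. The last stands in the outcome definition, so it is the one that would be applied.

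The composite is met only if every component is met. A child with all Bayley-IV domains at 85 or above and a normal examination therefore fails it on a parent's answer about hearing or sight. The parent can know whether the child was cooled. The definition states no check on that answer and no severity threshold.

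At stake is a modest reporting bias in a secondary outcome, and a description of the 2-year outcomes as assessed by a masked team that does not fit this component.

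**Working it through.** **Step 1. The passages side by side.**

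| Place | Source of hearing and vision status | Can the source know the allocation? |
|---|---|---|
| Assessment and follow-up, first paragraph | Detailed neurological examination at the masked team's visit | Examiners are masked |
| Assessment and follow-up, second paragraph | Medical history | Yes, if the history comes from parents; the article does not say who takes it |
| Secondary outcomes | Parent report | Yes |

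Two readings are possible.

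- The first paragraph promises an examination. The three statements then conflict and have to be reconciled.
- The assessment in the first paragraph is simply done by history. The wording conflict then disappears, but the component still rests on parents who can know the allocation.

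On either reading, the outcome as defined contains a component that is not masked.

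**Step 2. The plan's own figure, needed here only for the number per arm.** With a 5-point difference, SD 15, two-sided 0.05 and 90% power, the t-test calculation gives 190.1, rounded up to 191 per group. Allowing for 10% drop-out, 191 / 0.9 = 212.2, rounded up to 213 per group, or 426 in total. The plan's figures reproduce. They concern the primary score and are unaffected by this point.

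**Step 3. Possible size, by assumption only.** The article gives no rate for hearing or visual impairment and none for the composite. Let *p* be the true proportion meeting the composite in both arms (assumed 0.60 to 0.80). Let *e* be the share of those children wrongly reported as impaired in one arm only (assumed 0.01 to 0.05). Then:

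- shift in the composite = *p* × *e*
- standard error of the difference with 191 per arm and equal rates = √(2*p*(1 − *p*)/191)

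| *p* | *e* | Shift (percentage points) | Chance of a false significant result in that direction |
|---|---|---|---|
| 0.60 | 0.01 | 0.6 | 3.3% |
| 0.60 | 0.05 | 3.0 | 8.6% |
| 0.70 | 0.01 | 0.7 | 3.5% |
| 0.70 | 0.02 | 1.4 | 4.8% |
| 0.70 | 0.05 | 3.5 | 11.0% |
| 0.80 | 0.01 | 0.8 | 3.9% |
| 0.80 | 0.05 | 4.0 | 15.4% |

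The nominal one-directional rate is 2.5%. At *p* = 0.70 the standard error is √(0.42/191) = 4.7 points, so a shift of 0.7 to 3.5 points is 0.15 to 0.75 standard errors. The upper end needs 5% of unimpaired children to be misreported in one arm and none in the other. Nothing in the article suggests that, so the lower rows are the more plausible.

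**The case against.** **The wording conflict is thin.** Assessment and follow-up can be read as first listing what is covered and then saying how it is collected, with Secondary outcomes agreeing. That is a fair reading. It removes the contradiction but leaves the unmasked component in place.

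**The article is open about parent report.** The source is printed inside the outcome definition, and the abstract is a one-sentence summary. This stands against any suggestion that the trial intends to report the whole composite as masked; the article does not say so. It remains true that the summary makes no exception for this component.

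**The bias is likely to be small.** By two years, a hearing or visual impairment is usually an established diagnosis, which leaves less room for bias than a subjective rating. This stands. The misreporting shares in the working have no source in the documents.

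**A reader might infer that the primary outcome is compromised**, because parents giving the history could tell the Bayley examiner that the child was cooled. The documents do not support that as a finding. They do not say who takes the history or when. A condensed article may leave this to the full protocol or the manual of procedures, and asking whether a child hears and sees normally does not itself reveal the treatment. The order stated for the CBCL does not show that the history is unprotected. What remains is a possible route to disclosure that is cheap to close.

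**The remedy is partial.** Freedom from seizure disorder, in the same composite, has no stated source and may also rest on history. Visits may take place at home, and the article does not show that hearing and vision can be tested there. Both remarks stand. They favour allowing a records check as an alternative to examination, and they mean that the fix improves the composite without guaranteeing that it is fully masked.

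**Conclusion.** The point holds for one component of one secondary composite. Hearing and vision are described in three ways, and the outcome definition uses a source that can know the allocation. Survival without any neurological impairment is therefore not fully masked as defined, while the abstract describes masked assessment of the 2-year neurodevelopmental outcomes without exception. The Bayley-IV domains and the neurological examination remain examiner-rated.

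The size of any bias cannot be computed from the documents. It is probably small, on two assumptions: that sensory impairment is rare in mild encephalopathy, and that parents mostly report established diagnoses. The range of 0.6 to 4.0 percentage points depends wholly on the assumed inputs.

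The article does not show that the primary cognitive score is unmasked, and this point does not claim it. It is a minor correction, worth making because it is cheap.

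**What to change.** 1. Name one source for hearing and vision, in the same terms, in Assessment and follow-up and in Secondary outcomes. Either use the vision and hearing assessment already listed there, or use parent report confirmed against clinical records for the few children with a reported problem.
2. If unconfirmed parent report is kept, state that this component is unmasked, and qualify the summary of masked follow-up to match.
3. As a precaution, state that the medical history is taken after the Bayley-IV and the neurological examination, as is already arranged for the CBCL relative to the Bayley-IV. If the full protocol or manual already says so, nothing more is needed.

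The cost is some wording, a reordered visit and a small records check. The check presupposes access to the relevant records, which the article does not describe, so it should be confirmed with sites first. The sample size and the primary analysis do not change.
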